**Aim**

To determine the effectiveness of COVID-19 vaccines in people with immunocompromised conditions.

**Objectives**

- Examine the odds of COVID-19-related outcomes after vaccination with one, two, or three vaccines in people with immunocompromised conditions (within immunocompromised group comparison)
- Examine the odds of COVID-19-related outcomes after vaccination with one, two, or three vaccines in people with blood cancer compared with the general population (between immunocompromised group comparison)

**Primary analysis**

Nested matched case-control design including both vaccinated and unvaccinated populations

**Outcomes**

The outcomes of interest are the occurrence and odds of the below COVID-19-related severe events following one, two, or three doses of vaccines compared to those who have not received the vaccine.

- COVID-19 Hospitalisation (hospitalisation within 14 days of testing COVID-19 positive)
- COVID-19-related ICU admission (admission to intensive care during a COVID-19 hospitalisation)
- COVID-19-related Death (death within 28 days of COVID-19 positive or COVID-19 on death certificate)

Cases will be patients who have had COVID-19 hospitalisation or COVID-19-related death, and will be matched to controls who did not experience the outcome of interest. Patients who experienced COVID-19-related ICU admission will be a subset of the COVID-19 hospitalisation cases and therefore will not be matched separately.

**Exposure definition**

*COVID-19 vaccination:*

It is expected to take 14 days for an immune response to the vaccine to develop (ref 34 in main text). We will therefore consider the population exposed 14 days after vaccination. For the analysis we will consider the exposure periods as used in previous research, where there are sufficient numbers (ref 32 & 35 in main text). For the analysis, we will define *vaccination status* considering one to four doses of any COVID-19 vaccine and the indicative time periods since vaccination as follows, although these may be amended after assessing the distribution of the data:

- Unvaccinated
- Days (weeks) after 1^st^ dose
- 0-13 days (<2 weeks)
- 14-27 days (2 - <4 weeks)
- 28-41 days (4 - <6 weeks)
- 42+ days (≥6 weeks)
- Days (weeks) after 2^nd^ dose
- 0-13 days (<2 weeks)
- 14-41 days (2 - <6 weeks)
- 42-97 days (6 - <14 weeks)
- 98-153 days (14 - <22 weeks)
- 154-181 days (22 - <26 weeks)
- 182-272 days (26 - <39 weeks)
- 273+ days (≥39 weeks)
- Days (weeks) after 3^rd^ dose
- 0-13 days (<2 weeks)
- 14-41 days (2 - <6 weeks)
- 42-97 days (6 - <14 weeks)
- 98-125 days (14 - <18 weeks)
- 126-153 days (18 - <22 weeks)
- 154-181 days (22 - <26 weeks)
- 182-272 days (26 - <39 weeks)
- 273+ days (≥39 weeks)

The following vaccine types will also be considered, where numbers are sufficient:

- BNT162b2
- ChAdOx1
- mRNA-1273

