**Matching**

All cases who had the outcome will be matched with 10 controls who did not have the outcome on that date by matching on age, sex, calendar date and GP practice using incidence density sampling (ref 35 in main text). We will remove GP practice from the matching criteria if there is not a sufficient number of controls to match to each case in the blood cancer group.

We will undertake matching in the cohort of immunocompromised patients and the general population separately.

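### The date to which days since vaccination are counted is not stated; the implied outcome date lets cases who tested positive before day 14 count as failures in the early exposed windows

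*SAP*

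**What the plan says.** - **Exposure definition (SAP).** The rationale is "It is expected to take 14 days for an immune response to the vaccine to develop", and the rule drawn from it is "We will therefore consider the population exposed 14 days after vaccination". Days 0–13 after each dose form a separate level. The exposed windows start at days 14–27 and 28–41 after dose 1, and at days 14–41 after doses 2 and 3. The windows are called indicative. The section does not name the date at which the count of days ends.
- **Outcomes (SAP).** Hospitalisation is "hospitalisation within 14 days of testing COVID-19 positive". Death is "death within 28 days of COVID-19 positive or COVID-19 on death certificate"; the second route sets no time limit.
- **Matching (SAP).** Cases are "matched with 10 controls who did not have the outcome on that date", with calendar date as a matching factor and incidence density sampling.
- **Statistical analysis (SAP).** Follow-up is censored at the outcome. Previous SARS-CoV-2 infection is a covariate, with no reference date given.

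**The concern.** The separate level for days 0–13 is there to keep infections that precede the immune response out of the exposed windows. It does so only if days are counted to infection or, as a proxy, to the positive test. The only index date that the SAP offers is that of the outcome, which can come up to 14 or 28 days after the test. Those lags are as long as, or longer than, the first exposed window after dose 1. For example, a person who tests positive on day 5 after dose 1 and dies on day 25 would be a failure in the 14–27 day window, although the test came before the SAP expects any protection.

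Odds ratios by dose and time since dose are the main product of this study. Misplaced cases pull the early-window odds ratios towards 1, and the pull can differ between hospitalisation and death, so comparisons between outcomes and between early and later windows would be affected as well.

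**Working it through.** The SAP gives no effect size, event count or lag distribution, so there is no stated figure to reproduce. Two checks apply.

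**1. Reach, from the SAP's own figures.** The latest outcome day for a positive test on days 0–13 is 13 plus the maximum lag.

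- Hospitalisation: 13 + 14 = day 27. Such cases can fall anywhere in dose-1 days 14–27 and in the first half of days 14–41 after doses 2 and 3.
- Death by the 28-day route: 13 + 28 = day 41. Such cases can fall anywhere in dose-1 days 14–27 and 28–41, and anywhere in days 14–41 after doses 2 and 3.
- Windows from day 28 (hospitalisation) or day 42 (28-day death) receive none of them. Deaths by certificate alone have no such limit.

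**2. Size, under stated assumptions.** Assume a constant infection rate, OR 1.0 for tests before day 14, true OR 0.40 (VE 60%) from day 14, and the lag distributions below. For an outcome on day d, the test came before day 14 if the lag exceeds d − 14. Let p be the mean of P(lag > d − 14) over the window. Then OR = p × 1.0 + (1 − p) × 0.40.

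| Outcome, dose-1 window | Assumed lag (days) | p | OR | VE reads |
|---|---|---|---|---|
| Hospitalisation, 14–27 | uniform 0–7 | 3.5/14 = 0.25 | 0.25 + 0.75 × 0.40 = 0.55 | 45% |
| Hospitalisation, 14–27 | uniform 0–14 | 7/14 = 0.50 | 0.50 + 0.50 × 0.40 = 0.70 | 30% |
| Death, 14–27 | uniform 0–28 | 10.5/14 = 0.75 | 0.75 + 0.25 × 0.40 = 0.85 | 15% |
| Death, 28–41 | uniform 0–28 | 3.5/14 = 0.25 | 0.25 + 0.75 × 0.40 = 0.55 | 45% |

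The weight p is what would be seen with no vaccine effect. The share of observed cases that tested before day 14 is p/OR: for the two death rows, 0.75/0.85 = 88% and 0.25/0.55 = 45%.

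**Vaccination after a positive test.** In the third row, 0.25 of the 0.75 comes from people who tested positive before the dose was given. If nobody is vaccinated after a positive test, that part drops out while controls keep their doses: OR = 0.50 + 0.25 × 0.40 = 0.60, so VE reads 40%. The other rows do not change, because there the lag cannot reach back before the dose.

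**Doses 2 and 3.** Over days 14–41, hospitalisation with a lag uniform over 0–14 days has p = 7/28 = 0.25, so OR = 0.25 + 0.75 × 0.40 = 0.55 at most. It is an upper bound because earlier doses may protect before day 14.

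**Sensitivity to the lag.** A day-by-day calculation with true OR 0.30 gives, for hospitalisation on dose-1 days 14–27, an OR of 0.35, 0.47 and 0.65 at mean lags of 1.0, 3.5 and 7.0 days. The formula above gives the last of these too: 0.50 + 0.50 × 0.30 = 0.65. For death on days 14–41 it gives 0.40, 0.48 and 0.65 at mean lags of 4.0, 7.0 and 14.0 days, if vaccination after a positive test is allowed.

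**The case against.** - **The SAP nowhere says that status is read at the outcome date.** The Matching section fixes when controls must be free of the outcome, the Statistical analysis section fixes censoring, and both the windows and the sampling cite sources in a main text that is not at hand. This stands: the outcome date is implied, not stated. It does not remove the problem. Either the implied date is used and the early windows are contaminated, or the date is open and two analysts could report different early-window odds ratios.
- **Most windows are untouched, and they are only indicative.** True for the 14- and 28-day lags. A reader might infer that the whole time-since-dose profile is shifted; the day arithmetic does not support that.
- **The bias need not run in one direction.** Controls can gain a dose between the case's test and the outcome date when the ill case typically cannot. This lowers the odds ratio and raises apparent VE. It stands, and it is why the death figure moves from 15% to 40%.
- **The size rests on assumed lags.** It does. At a mean admission lag of 1 day the OR moves only from 0.30 to 0.35.
- **Previous infection.** A reader might infer that this covariate would pick up the case's own qualifying test. The SAP does not say so, and its cited definition is not shown. Only the lack of a reference date can be held against it.

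**Conclusion.** The point holds in this form: the reference date for vaccination status is not stated, and the date that the matching and censoring rules imply would defeat the SAP's own 14-day rule in the early windows. The reach follows from the SAP's figures alone.

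The size does not. With true VE of 60%, no protection before day 14 and the uniform lags assumed here, VE on dose-1 days 14–27 reads 30% to 45% for hospitalisation. For death it reads 15% to 40%, depending on whether anyone is vaccinated after a positive test. Shorter lags give less bias, and the effect after doses 2 and 3 is smaller because the window is wider and earlier doses may protect.

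Two stronger readings should be avoided. The 15% figure is not an expected result: it needs deaths spread evenly over 28 days and doses given after a positive test. The weights of 75% and 25% are not shares of observed deaths; those are 88% and 45% under the same assumptions.

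**What to change.** 1. State the index date of each matched set as the date of the case's positive test for the qualifying episode. Sample controls at that date, and read vaccination status and covariates there.
2. Count only infection episodes before the index date as previous infection.
3. For deaths identified by certificate alone, use the earliest COVID-19 record within the same episode, with a look-back limit stated in advance, and otherwise the date of death. Repeat the analysis without these cases, since the date-of-death fallback keeps the lag.
4. Align the censoring wording in the Statistical analysis section with the new index date.
5. Keep the version with status at the outcome date as a sensitivity analysis.

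The cost is SAP wording, some re-programming and the fallback rule. Test dates are already needed for the outcome definitions. Infections acquired before day 14 but tested later would still fall in the exposed windows; the change does not remove those.

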**Matching**

All cases who had the outcome will be matched with 10 controls who did not have the outcome on that date by matching on age, sex, calendar date and GP practice using incidence density sampling (ref 35 in main text). We will remove GP practice from the matching criteria if there is not a sufficient number of controls to match to each case in the blood cancer group.

We will undertake matching in the cohort of immunocompromised patients and the general population separately.

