**Statistical analysis**

People will enter the cohort on 01/12/2020 (start date) and censored on the earliest date of outcome of interest (hospitalisation, ICU admission, or death) or end of the study period 11/04/2022 (end date). Individuals with the outcome of interest before the study start date will be excluded from the primary analysis.

Conditional logistic regression models will be used to report odds ratios and 95% confidence intervals between vaccinated and unvaccinated groups, adjusting for covariates as listed below. Subgroups of immunocompromising conditions will also be examined using the same methods described above, provided there is sufficient data for analysis.

We will conduct stratified analyses by calendar time to account for different SARS-CoV-2 variants circulating in the UK. We will split calendar time into the following intervals (ref 36 in main text):

- Alpha: 18 Dec 2020 – 17 May 2021
- Delta: 18 May 2021 – 19 Dec 2021
- Omicron BA.1: 20 Dec 2021 – 1 March 2022

*Covariates*

- Previous SARS-CoV-2 infection (ref 37 in main text).
- Socioeconomic status as measured by the Townsend score
- Ethnicity
- BMI (consider multiple imputation for missing values)
- Co-morbidities: 36 underlying clinical conditions identified using the QCOVID risk algorithm, where available in the dataset (ref 32 in main text). Co-morbidities will be grouped as below and included in the model by the following categories:
- Cardiovascular conditions (atrial fibrillation, heart failure, stroke, peripheral vascular disease, coronary heart disease, congenital heart disease)
- Diabetes (type 1 and type 2)
- Respiratory conditions (asthma, rare respiratory conditions (cystic fibrosis, bronchiectasis, or alveolitis), chronic obstructive pulmonary disease, pulmonary hypertension or pulmonary fibrosis)
- Cancer (lung or oral cancer, marrow transplant, radiotherapy)
- Neurological conditions (cerebral palsy, Parkinson’s disease, rare neurological conditions (motor neurone disease, multiple sclerosis, myasthenia, Huntington’s chorea), epilepsy, dementia, learning disability, severe mental illness)
- Other conditions (liver cirrhosis, osteoporotic fracture, rheumatoid arthritis or systemic lupus erythematosus, sickle cell disease, venous thromboembolism, solid organ transplant, renal failure (CKD3, CKD4, CKD5, with or without dialysis or transplant))

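### A fixed 10 controls per case may cost precision in the immunocompromised cohort once unvaccinated people, the reference group, become rare

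*SAP*

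**What the plan says.** Under Matching, the SAP sets one ratio: "All cases who had the outcome will be matched with 10 controls who did not have the outcome on that date". The factors are age, sex, date and practice, and controls are drawn from the risk set at the time of each case. The ratio applies to both cohorts: "We will undertake matching in the cohort of immunocompromised patients and the general population separately". No reason for 10 is given.

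One rule covers a shortage of controls: "We will remove GP practice from the matching criteria if there is not a sufficient number of controls to match to each case". The sentence confines this to the blood cancer group. The SAP does not say whether a case with one to nine eligible controls is kept, and it has no plan for using more than 10.

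Under Outcomes, the events are studied after "one, two, or three doses of vaccines compared to those who have not received the vaccine". Under Statistical analysis, "Conditional logistic regression models will be used to report odds ratios and 95% confidence intervals between vaccinated and unvaccinated groups". Follow-up runs from 01/12/2020 to 11/04/2022. The exposure definition lists 19 intervals after a dose (4 after the first, 7 after the second, 8 after the third), subject to amendment once the data are seen. Calendar strata and condition subgroups divide the data further. The SAP states no case count, cohort size, uptake or target precision.

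**The concern.** The usual argument for a modest number of controls is that m controls per case keep m/(m+1) of the information in the full risk set, so 10 keep 10/11 = 91%. That holds at an odds ratio of 1. Here the reference may shrink to a few per cent of the risk set by the later strata, and the association is expected to be strong. Many sets of 11 would then contain no unvaccinated person and add nothing to the vaccinated-versus-unvaccinated contrast.

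At stake is the width of the confidence intervals in the immunocompromised cohort and its subgroups, where the SAP itself makes analyses conditional on sufficient data. The number of cases cannot be raised. The number of controls can, wherever more eligible people are in the records.

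**Working it through.** **The plan's own figure.** There is none to reproduce, because the SAP gives no precision or sample-size calculation.

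**Inputs.** From the SAP: m = 10 controls, unvaccinated as reference, conditional logistic regression. Assumed: p, the unvaccinated share among eligible controls, and ψ, the rate ratio for unvaccinated versus vaccinated, so that effectiveness = 1 − 1/ψ. The calculation takes a homogeneous risk set, a binary exposure and no covariates.

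**Formula.** The case is unvaccinated with probability q = pψ/(pψ + 1 − p), and the number unvaccinated among the controls is Binomial(m, p). For a set with k unvaccinated among m + 1 people, let w = kψ/(kψ + m + 1 − k). The information per set is the sum over k of P(k)·w(1 − w). Full risk-set information is q(1 − q). Efficiency is the ratio of the two, and the standard error is inflated by 1/√efficiency.

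**Check.** At ψ = 1 and m = 10 the formula returns 0.909 = 10/11.

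**Worked case, p = 0.05, ψ = 5 (80% effectiveness).**
- q = 0.25/(0.25 + 0.95) = 0.2083, and q(1 − q) = 0.1649.
- Information per set with 10 controls = 0.1203.
- Efficiency = 0.1203/0.1649 = 0.729, and 1/√0.729 = 1.171.

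**Range.**

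| Unvaccinated | Effectiveness | Efficiency, 10 controls | SE vs full risk set | Efficiency, 50 controls |
|---|---|---|---|---|
| 50% | 80% | 0.94 | +3% | 0.99 |
| 20% | 50% | 0.876 | +7% | 0.97 |
| 10% | 67% | 0.822 | +10% | 0.96 |
| 5% | 80% | 0.729 | +17% | 0.934 |
| 2% | 90% | 0.558 | +34% | 0.870 |

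**Sets with no unvaccinated member (5% unvaccinated, 80% effectiveness).** All 10 controls are vaccinated with probability 0.95^10 = 0.599. The case must be vaccinated too, with probability 1 − 0.2083 = 0.7917. The product is 0.474, so about 47% of whole sets are silent on the main contrast.

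**What this does to an interval.** Assume 100 cases, 5% unvaccinated and a true odds ratio of 0.2. With 10 controls the SE of the log odds ratio is 1/√(100 × 0.1203) = 0.288, and the 95% interval is 0.114–0.352. With 50 controls it is 0.121–0.330, and with the full risk set 0.123–0.324.

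**Several exposure intervals at once.** A simulation with unvaccinated people plus four vaccination intervals gives a similar picture. With 3–5% unvaccinated and interval odds ratios of 0.6 to 0.1, efficiency is 0.72–0.80 with 10 controls and 0.93–0.96 with 50. With 40% unvaccinated it is already 0.90–0.98 with 10.

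**When few extra controls exist.** At 5% unvaccinated and 80% effectiveness, efficiency is 0.765 with 12 controls and 0.804 with 15. Stopping at 10 then raises the SE by only √(0.765/0.729) = 1.02 or √(0.804/0.729) = 1.05.

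**The case against.** The strongest reply is that nothing is shown to be lost. Matching on age, sex, date and GP practice within the immunocompromised cohort may leave few candidates, and the SAP itself foresees too few in the blood cancer group. Where 10 or fewer are eligible, no information is left unused; at 12 or 15 the loss is 2% or 5% of the SE. Reaching 50 or more might require giving up GP practice, which trades precision against control of confounding by place. Uptake, cohort size and case numbers are not stated, so a rare reference is an assumption, and early in the study it may well be common. The SAP also cites a source for its sampling method that may explain the ratio.

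Most of this stands, and it limits the size of the point. The warning about GP practice does not count against the change proposed here, which keeps the matching factors as chosen and uses whoever is eligible.

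A reader might also infer that the SAP ignores a shortage of controls. It does not: it would drop GP practice. What remains is that the rule names only the blood cancer group and leaves unsaid what happens to a case that still has fewer than 10.

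**Conclusion.** The point holds as a conditional loss of precision and a cheap improvement. Where more than 10 eligible controls exist, stopping at 10 keeps about 56–88% of the full risk-set information if 2–20% are unvaccinated and effectiveness is 50–90%. At 50% unvaccinated and 80% effectiveness it keeps about 94%, so the gain early in the study is slight. These shares and effects are assumptions; the SAP supplies neither.

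Three stronger readings are not supported:
- That the odds ratios are biased or the plan contradicts itself. Under the sampling described they remain valid with 10 controls, and in the 100-case example the conclusion does not change.
- That information is certainly being thrown away. That depends on how many eligible controls matching leaves, which the SAP does not report.
- That 60% of sets are useless at 5% unvaccinated. The 60% describes groups of 10 controls. For whole sets the figure is about 47% at 80% effectiveness, and those sets can still inform contrasts between vaccination intervals.

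**What to change.** In the Matching section, for the immunocompromised cohort and its condition subgroups:
- keep the chosen matching factors and take all eligible risk-set members on the index date as controls, or a random sample up to a stated cap such as 50–100;
- allow variable set sizes and retain every case with at least one eligible control;
- state that matching will not be loosened merely to reach a target number, and revise the GP-practice rule to agree with this;
- report the distribution of controls per case and the unvaccinated share by calendar stratum.

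Keep 1:10 in the general population. The two cohorts are matched separately, so different ratios cause no difficulty, and conditional logistic regression accepts variable set sizes unchanged. The cost is SAP wording and more computing, with no new data or patients. Where matching leaves about 10 or fewer controls, the gain will be small.

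### If GP practice is dropped from the matching, the SAP names no broader area in its place, so same-date differences between areas have no direct control

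*SAP*

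**What the plan says.** The Matching section of the SAP sets the ratio: "All cases who had the outcome will be matched with 10 controls who did not have the outcome on that date". It names the factors and the sampling method in these words: "by matching on age, sex, calendar date and GP practice using incidence density sampling". It then gives the fallback: "We will remove GP practice from the matching criteria if there is not a sufficient number of controls to match to each case". The sentence ends by tying the trigger to the blood cancer group. It does not put a number on a sufficient supply of controls, and it does not say what replaces practice.

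On the two cohorts the same section says: "We will undertake matching in the cohort of immunocompromised patients and the general population separately". It does not say whether the fallback, once triggered, applies to one cohort or to both.

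The Statistical analysis section specifies the model: "Conditional logistic regression models will be used to report odds ratios and 95% confidence intervals between vaccinated and unvaccinated groups", adjusted for a covariate list. The entries nearest to geography are "Socioeconomic status as measured by the Townsend score" and ethnicity. The entry nearest to infection pressure is the person's own history, "Previous SARS-CoV-2 infection (ref 37 in main text"). Calendar time is also stratified by variant period for the UK as a whole.

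**The concern.** On any given date, areas differ both in how much infection is circulating and in how many people are vaccinated. Area is then a common cause of exposure and outcome. Matching on practice together with date deals with this, because a case is compared only with people from the same place on the same day. Once practice is removed, a case in a high-incidence area can be matched to controls from anywhere in the data.

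Two results are at stake. The first is the within-group odds ratio for vaccination (Objective 1), which could be shifted by local differences unrelated to vaccine effect. The second is the comparison of blood cancer with the general population (Objective 2), which needs the two odds ratios to be built in the same way. The text leaves open whether they would be.

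**Working it through.** The SAP states no sample size, event count or bias figure, so there is nothing of its own to reproduce. The check has four steps. Every figure in steps 2 to 4, other than the planned 10 controls, is an assumption or follows from one.

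**1. Is there any other location term?** The matching factors are age, sex, calendar date and GP practice. The covariates are previous infection, Townsend score, ethnicity, BMI, co-morbidities, medications and chemotherapy. None is a place, a local infection rate or a local uptake. The variant strata divide time, not area. GP practice is the only geographic control.

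**2. Could the fallback be triggered?** Expected eligible controls in one practice = list size × prevalence × 0.5 (same sex) × share in the age band, taking a blood-cancer-only pool.

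- Lowest: 5,000 × 0.003 × 0.5 × 1/60 = 0.1
- Middle: 10,000 × 0.005 × 0.5 × 1/20 = 1.25
- Highest: 20,000 × 0.01 × 0.5 × 1/10 = 10

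All but the most favourable combination give 5 or fewer. A shortage against the planned 10 is plausible.

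**3. What could follow from ignoring area?** Take two equal areas, A and B, with uptake uA and uB, incidence ratio RR (B to A) and true odds ratio ψ. Under incidence density sampling, the odds ratio that ignores area is

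[ψ(uA + uB·RR) / ((1−uA) + (1−uB)·RR)] ÷ [(uA + uB) / (2−uA−uB)].

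With ψ = 0.20 and uA = 0.95:

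| RR | uB | Case odds | Control odds | Odds ratio ignoring area |
|---|---|---|---|---|
| 2 | 0.90 | 0.55/0.25 = 2.20 | 1.85/0.15 = 12.33 | 0.178 |
| 2 | 0.85 | 0.53/0.35 = 1.51 | 1.80/0.20 = 9.00 | 0.168 |
| 3 | 0.90 | 0.73/0.35 = 2.09 | 12.33 | 0.169 |
| 3 | 0.85 | 0.70/0.50 = 1.40 | 9.00 | 0.156 |

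Effectiveness of 80% would appear as 82–84%. Over a wider grid (RR 1.25 to 3; uptake 95% v 90%, 95% v 85% or 90% v 75%) the ratio of apparent to true odds ratio runs from 0.96 to 0.78. At RR 2 and 95% v 85%, a true odds ratio of 1.00 appears as 0.84.

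If the higher incidence lies in the high-uptake area, the bias reverses. With RR = 2 and uB = 0.90 the case odds are 0.56/0.20 = 2.80, and 2.80/12.33 = 0.227.

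With area kept as a factor, the ratio is 1.00 in this model.

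**4. What would keeping practice with fewer controls cost?** For a binary exposure with m controls per case, the expected conditional information is I(m) = Σ P(k)·q(1−q), with q = kψ/(kψ + m + 1 − k). Here k is the number vaccinated in the set; controls are vaccinated with probability p and the case with probability ψp/(ψp + 1 − p). Relative CI width is √(I(10)/I(m)). For ψ = 0.20 and p = 0.90, I(10) = 0.1788 and I(5) = 0.1435, so the ratio is √1.246 = 1.12.

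| Vaccinated | 5 controls | 3 controls | 1 control |
|---|---|---|---|
| 85% | 1.10 | 1.23 | 1.75 |
| 90% | 1.12 | 1.26 | 1.83 |
| 95% | 1.13 | 1.29 | 1.91 |

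**The case against.** The strongest reply is that giving up practice in a rare-disease cohort is a reasonable trade of bias against variance, declared in advance. Much of this stands. Step 4 shows that sparse same-practice sets are expensive: CIs about 10–13% wider with 5 controls, 23–29% with 3 and 75–91% with 1. A reader might use the familiar efficiency m/(m+1) and infer a cost of only 4% with 5 controls and 10% with 3. That formula holds at an odds ratio of 1, not at a strongly protective effect. At an average of one eligible control per practice (Poisson), about 37% of cases would have none. So the SAP is not wrong to let practice go. The reply does not explain why nothing replaces it, since a broader area has far more candidates.

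Three other replies narrow the point:

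- **Trigger.** A reader might infer that the fallback is close to certain because 10 controls per practice can rarely be found. The SAP asks for a sufficient number, not explicitly 10, and gives no threshold. It also speaks of matching within the immunocompromised cohort, a larger pool than blood cancer alone. Step 2 supports plausible, not near-certain.
- **Control.** A reader might infer that local infection and uptake would be wholly uncontrolled. Date matching handles the national course of the epidemic; Townsend score and ethnicity partly track uptake, and previous infection weakly tracks exposure. Not directly controlled is the accurate description.
- **Asymmetry.** A reader might infer that only the blood cancer group would lose practice matching. Removal in both cohorts is an equally natural reading. This is an ambiguity to settle, not a stated design difference.

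**Conclusion.** The point holds as a gap in a rule that the SAP itself states. The fallback removes the only geographic control and names no substitute, so if it is used, same-date differences between areas in infection rate and uptake are left to partial proxies.

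Neither the size nor the direction of the bias can be derived from the document. The shift from 0.20 to 0.16–0.18 rests on a two-area model with assumed incidence and uptake and no covariate adjustment. It shows a modest distortion, in either direction, which the planned analysis could not detect. The likelihood of the fallback likewise rests on assumed list sizes, prevalence and age bands.

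The change is worth making because it is cheap and reduces a foreseeable bias. It is not a finding that the planned estimates would be seriously wrong.

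**What to change.** Replace the fallback sentence with a step-down rule:

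1. State what counts as too few controls.
2. If practice matching fails that test, match instead on a broader area, the region or local health area of the practice, together with age, sex and calendar date, keeping up to 10 controls per case.
3. If area cannot be a matching factor, add region as a covariate. Matching on area and date together is preferable, because a single region term captures only an average difference over the study, while local epidemics rise and fall at different times.
4. Apply the same rule in the immunocompromised and general-population cohorts, so that the Objective 2 comparison rests on the same matching.
5. Report the number of controls per case in each cohort.

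The cost is SAP wording and a small change to the sampling program. Control of area will be coarser than practice, so some local confounding may remain. The justification should not claim that keeping practice with only a few controls is nearly free.

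### Objective 2 compares blood cancer with the general population, but the SAP specifies no between-group contrast: it yields separate vaccination odds ratios and nothing that compares them

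*SAP*

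**What the plan says.** The Objectives section lists two aims. The first is a comparison within the immunocompromised group. The second concerns the odds of COVID-19 outcomes after one, two or three vaccines "in people with blood cancer compared with the general population (between immunocompromised group comparison").

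The sections that would deliver the second aim read as follows.

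- Outcomes: events are considered "following one, two, or three doses of vaccines compared to those who have not received the vaccine".
- Matching: "All cases who had the outcome will be matched with 10 controls who did not have the outcome on that date", and "We will undertake matching in the cohort of immunocompromised patients and the general population separately".
- Statistical analysis: "Conditional logistic regression models will be used to report odds ratios and 95% confidence intervals between vaccinated and unvaccinated groups". Then: "Subgroups of immunocompromising conditions will also be examined using the same methods described above, provided there is sufficient data for analysis".
- Statistical analysis, on stratification: "We will conduct stratified analyses by calendar time to account for different SARS-CoV-2 variants circulating in the UK".

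The covariate list has no cohort or blood-cancer term. The SAP contains no interaction, ratio of odds ratios, heterogeneity test or model spanning the two cohorts.

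**The concern.** The SAP states an objective and a model, and the two do not meet. Objective 2 is a comparison between groups, whereas every planned estimate is a comparison within a group. An analyst who follows the text will have a table of vaccination odds ratios for blood cancer and another for the general population, with nothing that says how far apart they are or how precisely that is known.

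The wording of objective 2 also allows two different questions: whether vaccination works less well in blood cancer, and whether people with blood cancer fare worse at the same vaccination status. These need different control sampling. If the SAP does not choose, the choice may be made after results are seen. The Exposure definition lists 19 time-since-dose categories (4 after the first dose, 7 after the second, 8 after the third), so there is also wide room to select which differences to discuss.

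**Working it through.** The SAP gives no event counts, standard errors or power, and the main check needs none.

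**1. What the matched sets can estimate.** Take a set of one case (j = 1) and ten controls (j = 2 to 11). Let v be vaccination status and z be cohort (1 = blood cancer, 0 = general population), leaving other covariates aside. The set contributes

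exp(βv₁ + γz + δv₁z) / Σⱼ exp(βvⱼ + γz + δvⱼz).

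Matching is done separately in each cohort, so z is the same for all eleven members. The factor exp(γz) cancels, leaving

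exp((β + δz)v₁) / Σⱼ exp((β + δz)vⱼ).

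- γ, the direct log odds ratio of blood cancer against general population, has disappeared and cannot be estimated.
- β is the vaccination log odds ratio in the general population, and β + δ is that in blood cancer.
- δ = ln(OR in blood cancer) − ln(OR in general population) remains estimable. exp(δ) is the ratio of odds ratios.

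This assumes that the general-population cohort contains nobody with blood cancer. The SAP does not say so, and the protocol may. If it did contain such people, some sets could be mixed, but the model would still have no blood-cancer term.

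**2. What the plan reports.** The planned models give β and β + δ in separate fits. No section asks for δ, its interval or a test. The subgroup sentence repeats the vaccinated-versus-unvaccinated method, and the only stratification is by variant period.

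**3. What reporting the ratio would cost in precision.** If the cohorts do not overlap, SE(δ) = √(s₁² + s₂²), where s₁ and s₂ are the standard errors of the two log odds ratios. The values below are assumptions, with s₁ = 0.25 for blood cancer throughout. The blood-cancer half-width alone is 1.96 × 0.25 = 0.490.

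| s₂ (general population) | SE(δ) | 95% half-width of δ | Relative to 0.490 |
|---|---|---|---|
| 0.05 | √0.0650 = 0.255 | 0.500 | 1.02 |
| 0.10 | √0.0725 = 0.269 | 0.528 | 1.08 |
| 0.25 | √0.1250 = 0.354 | 0.693 | 1.41 |

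The larger the general-population cohort, the closer the ratio's precision comes to that of the blood-cancer odds ratio itself.

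**The case against.** The strongest reply is that objective 2, read with the Outcomes section, most naturally asks how vaccination odds ratios in blood cancer compare with those in the general population. Separate matching is a sound design for that question, and the contrast can be recovered from planned output by subtracting log odds ratios. This stands. A reader might infer that separate matching makes objective 2 impossible to estimate. That is true only of the direct cohort odds ratio, and the matching sentence is not itself an error.

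It can also be said that blood-cancer odds ratios are covered by the subgroup sentence, that the Matching section mentions a blood cancer group, and that variant-period stratification already deals with calendar time in broad terms. These points stand in part. Age matching, however, removes confounding within a cohort and does not equalise age mix between cohorts. If the vaccine effect varies with age, some of that would enter the ratio. The SAP gives no figures to size this.

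A reader might also suppose that the two sets would be judged by whether their confidence intervals overlap, and measure the harm by how conservative that rule is (at equal standard errors it demands a difference √2 = 1.41 times that of a direct test). The SAP proposes no such rule, so this does not measure a fault in the plan.

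The objection does not supply the contrast. That a quantity could be derived is not the same as specifying it, and the SAP neither names it nor ensures that the two sets of odds ratios are comparable.

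**Conclusion.** The point holds as a gap in specification. One of the SAP's two objectives has no between-group estimate, interval or test behind it, for any dose category. The direct odds ratio of blood cancer against general population is not estimable from separately matched sets. The ratio of vaccination odds ratios is, with no change to the sampling.

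The conclusion follows from the structure of the SAP and does not depend on the assumed standard errors, which serve only to show the cost in precision. It assumes non-overlapping cohorts and blood-cancer sets formed within the blood-cancer group. The documents do not support the wider claims that objective 2 is out of reach or that a flawed comparison method has been chosen.

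**What to change.** State in the SAP that the estimand of objective 2 is the ratio of vaccination odds ratios, blood cancer over general population. Then:

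- Stack the blood-cancer and general-population matched sets in one conditional logistic model with vaccination status × cohort terms and cohort-specific covariate effects. Equivalently, take the difference in log odds ratios with SE = √(s₁² + s₂²) if the cohorts do not overlap.
- Report the ratio with a 95% confidence interval by dose category, overall and within the planned variant periods where numbers allow.
- Use the same exposure categories in both cohorts, since the Exposure definition allows them to be amended after the data are seen. Use the same matching factors too, since the Matching section allows GP practice to be dropped because of the blood cancer group without saying whether this applies to both cohorts.
- Confirm that the two cohorts do not overlap, and that the comparison group is blood cancer rather than all immunocompromised patients.

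The cost is SAP wording, one additional model, and wider intervals on the ratio than on either odds ratio alone. Ratios by age band or standardised to the blood-cancer case mix are optional and may be sparse.

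If the intended question is relative risk at equal vaccination status, the SAP should say so. That needs controls sampled across both cohorts with blood cancer as an exposure, which is new sampling and not merely an extra model.
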